## Abstract

**Background:**

Sleep problems are common, affecting over a third of adults in the United Kingdom and leading to reduced productivity and impaired health-related quality of life. Many of those whose lives are affected seek medical help from primary care. Drug treatment is ineffective long term. Psychological methods for managing sleep problems, including cognitive behavioural therapy for insomnia (CBTi) have been shown to be effective and cost effective but have not been widely implemented or evaluated in a general practice setting where they are most likely to be needed and most appropriately delivered. This paper outlines the protocol for a pilot study designed to evaluate the effectiveness and cost-effectiveness of an educational intervention for general practitioners, primary care nurses and other members of the primary care team to deliver problem focused therapy to adult patients presenting with sleep problems due to lifestyle causes, pain or mild to moderate depression or anxiety.

**Methods and design:**

This will be a pilot cluster randomised controlled trial of a complex intervention. General practices will be randomised to an educational intervention for problem focused therapy which includes a consultation approach comprising careful assessment (using assessment of secondary causes, sleep diaries and severity) and use of modified CBTi for insomnia in the consultation compared with usual care (general advice on sleep hygiene and pharmacotherapy with hypnotic drugs). Clinicians randomised to the intervention will receive an educational intervention (2 × 2 hours) to implement a complex intervention of problem focused therapy. Clinicians randomised to the control group will receive reinforcement of usual care with sleep hygiene advice. Outcomes will be assessed via self-completion questionnaires and telephone interviews of patients and staff as well as clinical records for interventions and prescribing.

**Discussion:**

Previous studies in adults have shown that psychological treatments for insomnia administered by specialist nurses to groups of patients can be effective within a primary care setting. This will be a pilot study to determine whether an educational intervention aimed at primary care teams to deliver problem focused therapy for insomnia can improve sleep management and outcomes for individual adult patients presenting to general practice. The study will also test procedures and collect information in preparation for a larger definitive cluster-randomised trial. The study is funded by The Health Foundation.

**Trial Registration:**

ClinicalTrials.gov ID ISRCTN55001433 –

## Background

Insomnia and sleep problems are common, affecting over a third of adults in the United Kingdom.[1,2] Many of those whose lives are affected seek medical help from primary care.[3] A review of cost effectiveness studies of diagnosis and treatment of insomnia highlighted that insomnia has a high economic cost on society, particularly in terms of productivity loss and impaired health-related quality of life.[4]

General practitioners and nurse prescribers have been shown to have a limited repertoire of responses (sleep advice sheet, prescription) when managing new patients or reviewing those with insomnia. Clinical responses are shaped by unduly positive attitudes towards newer hypnotics[5] and limited by lack of knowledge of alternative non-pharmacological approaches. This leads to management strategies that often involve the prescription of hypnotic drugs, despite the finding that GPs hold less than favourable views of these drugs overall.[6] Evidence also suggests that hypnotic prescribing fosters patient dependency and passive 'help seeking behaviour' involving further requests for prescriptions. The clinical benefits of hypnotics are small and short-lived. They also carry significant risks of adverse events, for example increases in risk of falls, fractures,[7] depression[8], suicide[9] and excess mortality.[10] These dangers are particularly pronounced in the elderly who are most vulnerable to potential harm.[11] A compelling case exists for both improving quality of care for these patients and doing so by encouraging changes in prescribing, although there is less evidence about how to achieve these outcomes.

We could find no published evidence on the costs of poor sleep in the UK. However in the US the costs (direct, indirect and related) of insomnia have been estimated at US$30 to 35 billion per annum (1994 US$) [12] and in Australia AUS$7494 million (2004 AUS$) of which 53% was accounted for by work-related injuries (net of health costs), private motor vehicle accidents (net of health costs) and productivity losses associated with sleep disorders.[13] The review by Martin et al.[4] made three research recommendations encompassing the need for more accurate costs for patients with different types of insomnia related diagnosis, an estimate of the health utilities associated with particular insomnia diagnoses and their treatments and finally to undertake cost utility analyses of treatments for insomnia to encourage resource allocation to this area.

We have shown in modelling studies involving patients, practitioners and practices that despite patients trying various self-help remedies and sometimes expecting a prescription when presenting with sleep problems, they also welcome a consultation approach which includes careful assessment and advice about non-pharmacological methods rather than a prescription. [14-16] Practitioners are generally positive towards finding new approaches that enhance their skills in non-pharmacological management methods. Brief psychological/behavioural methods[17] have also been shown to be effective in one previous limited evaluation of effectiveness.[18]

The objective of this paper is to describe the design of a pilot cluster randomised controlled study, the aim of which is to test procedures and collect information in preparation for a larger definitive cluster-randomised trial. The definitive study will determine the effectiveness and cost-effectiveness of an educational intervention for general practitioners, primary care nurses and other members of the primary care team to deliver problem focused therapy to adults patients presenting with sleep disturbance due to primary insomnia or specific comorbid insomnia due to pain or mild to moderate depression and anxiety compared to usual care (general advice on sleep hygiene and pharmacotherapy).

The team includes a general practitioner, psychologist, psychiatrist, qualitative researcher, statistician and health economist and a service user representative who have worked together undertaking studies of sleep management in primary care and have contributed to the rationale and design of this study.

## Methods

### Aims

Our main aim for the pilot study is to test procedures and collect information in preparation for a larger definitive cluster-randomised trial. The definitive trial will investigate the effectiveness and cost-effectiveness of a brief practice-based educational intervention (2 × 2 hours) for practice teams (GPs, primary care nurses and practice managers) to provide problem focused therapy for insomnia in adults involving the use of sleep assessment tools (assessed with standardised instruments and sleep diaries) and modified CBTi on sleep outcomes compared to usual care (general advice on sleep hygiene and pharmacotherapy). The study will include new patients presenting with primary and specific comorbid insomnia as well as patients with chronic insomnia on treatment.

The research question for the pilot trial is "How well do the procedures and processes designed for conduct of the trial lead to effective implementation of trial including recruitment, randomisation, intervention, and outcome measurements."

The research question for the main trial is as follows "How effective and cost-effective is an educational intervention to primary care teams (general practitioners, primary care nurses and practice managers) to deliver problem focused therapy to adult patients presenting with sleep problems due to lifestyle causes, pain or mild to moderate depression on sleep and quality of life compared with treatment as usual including sleep hygiene and pharmacotherapy?"

The primary hypothesis for the main trial to be addressed is:

"Education for primary care teams in problem focused therapy for patients presenting to primary care with insomnia leads to better sleep outcomes for patients compared to treatment as usual with sleep hygiene up to 3 months from the beginning of treatment."

Secondary hypotheses for the main trial include: "Education for primary care teams in problem focused therapy for patients presenting to primary care with insomnia improves daytime sleepiness, anxiety and depression, health-related quality of life and reduces hypnotic use, adverse effects and costs compared to treatment as usual including sleep hygiene."

### Study design

This study will be a pilot in preparation for a larger cluster-randomised trial. The purpose of undertaking this pilot will include testing the integrity of study protocol, recruitment and consent issues, outcome selection, data collection procedures, the randomisation procedure, and the acceptability of the intervention and determining a more accurate sample size.

A flow diagram summarizing recruitment and follow-up of physicians and patients is shown in Figure 1. We will undertake a pilot cluster randomised controlled trial (RCT) in which general practices are the unit of randomisation and where data will be collected from patients. Recruited general medical practices will be randomised to one of two arms: *intervention *consisting of education of primary care teams to use Problem Focused Therapy for insomnia comprising sleep assessment tools (sleep diaries and Insomnia Severity Index) and modified CBTi (mCBTi); or a *control *arm using treatment as usual (TAU). We will follow the CONSORT statement extension on conduct and reporting of cluster randomised controlled trials.[19]

**Figure 1 F1:**
[figure not shown]
**Consort diagram**.

### Participants

#### The Practices

We will recruit four practices from Lincolnshire Teaching Primary Care Trust using EMIS or SystemOne computer systems. Each practice will need to recruit at least 20 patients, based on the sample size calculation for a definitive RCT who meet the inclusion criteria in order to achieve the estimated sample size of 80 patients. Practices will be randomised to intervention and control groups once the practices have been recruited but allocation will be concealed until after patients have been recruited in order to reduce bias in selection and recruitment of patients to intervention and control practice.[20] Invitation letters will be sent out to all practices in Northwest Lincolnshire (40 practices) inviting participation. Patients will be recruited from practices that agree to participate.

#### Study population

Intervention and controls patients will include adults aged 18 years and over with primary or specific secondary (comorbid) insomnia having a Pittsburgh Sleep Quality Index (PSQI) of 5 or above and screened by a trial nurse for the following inclusion and exclusion criteria[21].

#### Inclusion criteria

1. At least 18 years old.

2. Difficulty initiating and/or maintaining sleep for 1 month or more verified by PSQI score of ≥5.

3. New presentations with insomnia and existing patients on long term hypnotics, over the counter or complementary therapies.

4. 1–3 above and sleep disrupted by painful conditions.

5. 1–3 above and depression measured by the Beck Depression Inventory (BDI score 11–30).

#### Exclusion criteria

1. Current or previous illicit substance or alcohol abuse.

2. Pregnant or planning pregnancy in the next 12 months

3. Psychotic illness and severe depression defined by a BDI score ≥ 31.

4. Documented or active symptoms of sleep disruptive comorbid conditions e.g. restless legs syndrome and any type of parasomnia.

5. Obstructive sleep apnoea.

6. Terminal Illness.

7. Inability to consent.

8. Current participation in another research study.

#### Participant recruitment

Eligible patients will be recruited by the GP, practice nurse or self referred (via a poster in the GP waiting room). After reading an information leaflet potential participants will register their interest to take part in the trial using a tear-off slip (see Figure 2).

**Figure 2 F2:**
[figure not shown]
**Participant recruitment flowchart**.

At least 48 hours after and within 10 working days of registering their interest, patients will be telephoned by the trial nurse (this is a practice based nurse trained to recruit and consent patients) to explain the study and check whether they still wish to participate. If the patient is interested the trial nurse will assess the patient against the above listed inclusion and exclusion criteria. Information will be recorded on a standard proforma including, for patients either not eligible or not willing to be recruited, the reason for ineligibility or for declining. Patients meeting the criteria will be sent an invitation by post to an initial assessment visit together with a copy of the Patient Information Sheet (PIS), consent form and baseline demographic questionnaire.

When the patient attends for the initial assessment a (practice based) trial nurse will discuss the PIS with the patient and gain informed consent. The PSQI and BDI will be carried out and checked against the inclusion and exclusion criteria requirements.

If the patient is fully eligible and informed consent is obtained the participant will be entered into the trial. The trial nurse will register the patient with the Trial Centre via a Safehaven fax system. The patient will be allocated a unique trial number by the trial centre. The trial nurse will inform the patient's GP that they have been entered into the trial. The rest of the baseline assessments will be performed at this stage (EuroQol EQ-5D, ESS, ISI, Sleep Diary, and PSYCHLOPS). An appointment will be made for the GP or practice nurse to begin assessment/treatment within 10 working days of the practice being allocated to either the intervention or control group or in the intervention practices, after training of the practice teams on problem focused therapy for insomnia.

Recruitment is planned to take place over 3 months using the methods described above including posters in GP waiting rooms and reminders to GPs and nurses supported by an information leaflet. During the recruitment phase patients will continue to receive treatment as usual.

### Intervention general practices

The intervention will consist of two two-hour educational sessions, using a previously published model of academic detailing to primary care teams.[22] GPs, practice nurses and practice manager will be invited to participate. The importance of all members of the team, including practice managers being involved is due to the key need, demonstrated in the modelling studies, for management support in developing the pathway of care within practices. The first session will include the background to the study, trial structure and procedures, assessment of sleep problems including the use of sleep assessment tools and measurements and information on sleep hygiene. The second session will be on the use of problem focused therapy in the consultation which includes careful assessment (using assessment of secondary causes, sleep diaries and severity) and modified cognitive behavioural therapy for insomnia. This session will also involve practice teams designing their own pathway for care. The timing and number of educational sessions is based on previous modelling studies with a group of 8 practices.

### Control general practices

The control practices will also receive the first session of training which will include the background to the study, trial structure and procedures, assessment of sleep problems including the use of sleep assessment tools and measurements and information on sleep hygiene. They will continue their usual practice (treatment as usual) supported by a standard sleep hygiene leaflet. In the UK, treatment as usual consists of advice on sleep hygiene (with or without a patient information leaflet) and hypnotic pharmacotherapy. We will provide advice on sleep hygiene and a sleep hygiene leaflet for control practices. Sleep hygiene consists of a good bedtime routine, avoiding alcohol, caffeine and nicotine and ensuring a comfortable sleeping environment.

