### Audit of interventions and activity

Primary care teams in the intervention practices will be required to send all clinicians and the practice manager to the educational sessions. Further educational sessions will be provided to clinical staff newly recruited during the study period as the need arises. GPs and nurses in intervention and control practices will record patients who present with insomnia and their use of sleep assessment and problem focused therapy techniques using practice computer systems. The content and usefulness of training will be assessed using questionnaires to those in receipt of training. Intervention and control practices will be audited on implementation of the educational intervention by measuring use of assessment and CBTi techniques used by undertaking a weekly computer Read codes audit of all patients recorded with insomnia as well as asking patients through telephone interviews. A sample of up to 4 patients and practitioners from each practice will be invited for a short telephone interview (20 minutes) to understand in more depth the interventions that have been delivered and received as well as perceptions towards these. The interview will determine fidelity to the intervention in study practices and contamination in the control practices and therefore will not be blinded.

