This study will undertake cost-effectiveness and cost utility analyses. Both types of analyses enable technical efficiency questions to be addressed, that is to ask, is an educational intervention for health professionals a cost effective way in which to improve the management of patients with sleep problems? In addition, cost-utility analysis will also enable allocative efficiency questions to be addressed within the health sector, for instance, is the brief educational intervention about CBTi considered in this study cost-effective compared to a diverse range of other health interventions or services? This study will estimate the cost-effectiveness in terms of cost per 1 point change on the Pittsburgh Sleep Quality Index (PSQI) and the cost utility using the EuroQol EQ-5D [26] to estimate the cost per QALY over the trial period. Both outcome instruments will be administered at baseline and 13 weeks to observe if change occurs as a result of the intervention and whether it is sustained.

The timeframe for the economic analysis will be that of the trial period. The change in costs will be divided by the change in effectiveness in order to estimate the cost effectiveness of the brief educational intervention compared to no brief educational intervention for health professionals. If non-dominance occurs (that is if costs are greater and the intervention is more effective or if the intervention is cheaper and less effective) an incremental cost-effectiveness ratio (the ratio of change in cost divided by change in benefit) will be produced. The confidence region around the incremental cost effectiveness ratio will be estimated using appropriate statistical techniques. Since this economic evaluation is being undertaken alongside a cluster randomised trial the analysis needs to reflect the increased uncertainty of randomising clusters rather than individuals, a number of approaches have recently been proposed each found to generate similar findings.[34] The stochastic analysis will enable a cost effectiveness acceptability curve to be produced [35] illustrating the decision uncertainty, that is the probability that the brief educational intervention for health professionals on improving sleep management is cost-effective compared to no educational intervention/usual care for a range of willingness to pay per QALY values.

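### Control practices receive session one of the two-session training, so the trial cannot estimate the economic comparison against no educational intervention that the article states

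*Protocol article*

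**What the plan says.** Intervention general practices defines the package: "The intervention will consist of two two-hour educational sessions, using a previously published model of academic detailing to primary care teams". It then describes the opening session: "The first session will include the background to the study, trial structure and procedures, assessment of sleep problems including the use of sleep assessment tools", followed by sleep hygiene. The second session covers problem focused therapy in the consultation: careful assessment (secondary causes, diaries, severity), modified CBTi, and each team's design of its own care pathway.

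Control general practices then states: "The control practices will also receive the first session of training which will include" the same list of topics. These practices otherwise continue as usual, supported by a sleep hygiene leaflet.

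Study design describes the intervention as education to use "Problem Focused Therapy for insomnia comprising sleep assessment tools (sleep diaries and Insomnia Severity Index) and modified CBTi (mCBTi"), set against a control "arm using treatment as usual (TAU").

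Health economic analysis frames the cost-effectiveness estimate as "the brief educational intervention compared to no brief educational intervention for health professionals". It describes the acceptability curve as the probability that the intervention "is cost-effective compared to no educational intervention/usual care for a range of willingness to pay per QALY values".

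On process measures, Audit of interventions and activity says "GPs and nurses in intervention and control practices will record patients who present with insomnia and their use of sleep assessment", together with their use of problem focused techniques. Telephone interviews are to judge fidelity in the intervention arm and contamination in controls.

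**The concern.** The comparator named in the economic analysis is not the one that the design provides. Control clinicians are trained in one of the two sessions that define the intervention, and that session includes sleep assessment tools, which Study design lists as part of the intervention. Any benefit of session one is present in both arms and cancels in the comparison.

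Two things are at stake. First, a ratio and an acceptability curve described as education against no education would be read by commissioners as the value of the whole 2 × 2 hour package, when the trial data speak only to its second half. Second, use of assessment tools in control practices is partly what the trial taught them. Unless it is separated from use of therapy techniques, the contamination findings of a pilot meant to test procedures are hard to interpret.

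**Working it through.** The point rests on no published figure, so there is none to reproduce. The check compares sections and adds one line of arithmetic.

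**1. How the control arm is described**

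| Section | Comparator |
|---|---|
| Abstract, Methods and design | Usual care, reinforced by sleep hygiene advice; no training session mentioned |
| Aims (primary hypothesis) | Treatment as usual, with sleep hygiene |
| Study design | Treatment as usual |
| Control general practices | Session one and a leaflet, on top of usual practice |
| Health economic analysis | Usual care by GPs and nurses; later, an arm without the education |

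Control general practices also says what usual treatment means in the UK: sleep hygiene advice, with or without a leaflet, and hypnotics. Training of clinicians in assessment tools is not in that definition, so the control arm exceeds the article's own account of usual care.

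**2. Training contact**

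Inputs: two sessions of two hours each (Intervention general practices); controls receive the first (Control general practices).

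- Intervention: 2 × 2 h = 4 h
- Control: 1 × 2 h = 2 h
- Difference between arms: 4 − 2 = 2 h, which is session two
- Difference implied by a comparator without education: 4 − 0 = 4 h

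**3. Consequence for cost, if controls were charged nothing**

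Let c1 and c2 be the delivery costs of the two sessions. The article gives neither.

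- Incremental delivery cost that matches the randomised effect: (c1 + c2) − c1 = c2
- Incremental delivery cost against no training: c1 + c2
- Ratio of the two: (c1 + c2)/c2 = 1 + c1/c2

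With c1 = c2 the ratio is 1 + 1 = 2. If session one cost half as much as session two, it would be 1 + 0.5 = 1.5. This concerns delivery only. Development cost, which the Health economic analysis section also counts, and the extra sessions for newly recruited staff are not split by session. The share of training in total cost is not given, so the effect on the whole ratio cannot be worked out.

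**4. If session one is costed in both arms**

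The ratio then matches the effect, but it answers a different question from the one stated. On either costing, the wording of the economic comparison needs to change.

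**The case against.** The control arm is not hidden. Control general practices states the session and the leaflet openly, and the abstract mentions reinforcement. The claim of a comparator without education appears only in Health economic analysis, once joined to usual care. Usual care reinforced by shared training is a legitimate comparator. Part of session one is study background and procedures, which both arms need. All of this stands, and it is why the remedy leaves the design alone. It does not reconcile the economic wording with the control arm.

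Some stronger readings are tempting, and the documents do not support them:

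- *The ratio will be wrong by a factor of two.* No section says that control training is costed at zero. The economic section uses the change in costs, and costing session one in both arms fits its text. The twofold figure is conditional.
- *The assessment component is wholly shared between arms.* Session two also teaches careful assessment with diaries and severity, to the intervention arm only. The overlap is partial. The primary hypothesis concerns education in problem focused therapy, which is mainly the subject of session two.
- *The definitive trial inherits an effect size for another comparison, or loses power.* Nothing says that its control arm would differ. Its sample size rests on a 1-point PSQI difference, not on a pilot estimate, and no figure for dilution is given.
- *The audit counts taught behaviour as contamination.* The audit names assessment and CBTi techniques as two categories, and contamination is to be judged from interviews. The gap is that the article does not say that assessment use is to be set aside.
- *Assessment training should be removed from the control session.* That is a design trade-off, not a correction.

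**Conclusion.** The point holds as a mismatch between design and stated comparator. The trial contrasts session two added to session one (4 h against 2 h) and cannot estimate education against none, which is what the ratio and acceptability curve are said to show. Plain treatment as usual, the label in Study design, is also inexact.

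The possible overstatement of incremental delivery cost is 1 + c1/c2, or twofold. The twofold figure rests on two assumptions that are not in the article: that controls are charged nothing for training, and that the two sessions cost the same. The comparator mismatch itself needs neither assumption. The economic evaluation is meant for the main trial, with its methods piloted here, so this is the stage at which to settle the comparator.

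**What to change.** Keep the design and change the text and the costing rule:

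- Name the comparator as usual care enhanced by session one and a sleep hygiene leaflet in the Abstract, Aims, Study design and Health economic analysis.
- Cost session one in both arms. Cost the leaflet in each arm that is given it; the article mentions it only for controls, so supply to intervention practices should be stated.
- State the cost-effectiveness ratio, the acceptability curve and the conclusions against that comparator.
- In the audit and interviews, report use of assessment separately, and count only problem focused therapy and modified CBTi techniques as contamination in controls.

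The cost is a few changes of wording and one costing rule, with no new data. The price is a narrower conclusion: the trial speaks to the added value of session two, and not to the value of the full 2 × 2 hour package against no education.
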